## 6.4 OHIP-G14 questionnaire

After oral examination, the person is given another questionnaire to reflect the perceived oral health-related quality of life. Therefore the validated OHIP-G14 questionnaire is used. The person is asked to fill this out truthfully and intuitively as well. Alternatively, questionnaire will be discussed in interview.

## 6.5 Documentation

Pseudonymous data collection will be carried out with a patient/control identification list (see appendix), a questionnaire to be filled in manually (see appendix) and two questionnaires to be filled in manually (see appendix). Paper-based questionnaire will be converted into a digital Excel form.

## 6.6 Data analysis

Data will be analysed with regard to individual oral health parameters for each patient/control person. Parameters are also evaluated separately for paretic and non-paretic side of patients mouths and for left and right side of controls in order to be able to make a side-by-side comparison.

With data from questionnaires, an evaluation is carried out for each question asked individually.

In addition, data is evaluated according to age, gender, form, duration and cause of facial nerve palsy.

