# Abbreviations

| API | approximal plaque index |
| --- | --- |
| MPD | maximum probing depth |
| mod. SBI | modified sulcus bleeding index |
| OHIP-G14 | Oral Health Impact Profile-Germany 14 |
| PBI | papillary bleeding index |
| PSI | periodontal screening Index |
| TI | Turesky plaque index |

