## 3.2 Secondary objective

Secondary objective is to determine oral health-related quality of life of patients with the validated OHIP-G14 questionnaire, in order to be able to address the psycho-social component of disease. Results of questionnaires are compared with variables of facial nerve palsy, such as duration and cause of disease, which are collected as part of routine examination of Jena Facial Nerve Centre, as well as with values of a control group.

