## 6.7 Comparison of results

Data are first compared between patients and secondary with those of controls.

Comparisons are made with regard to oral health parameters:

- per patient:

- paretic and non-paretic side of mouth

- per controls:

- right and left side of mouth

- between patients:

- both halves of total mouth

- paretic side of mouth

- non paretic side of mouth

- between patients and controls:

- both sides of total mouth

- paretic side of mouth with corresponding side of mouth of control person

- non-paretic side of mouth with corresponding side of mouth of control person

- compared in terms of data from questionnaires:

- answers to each question between patients

- answers to each question between controls

- answers to each question between patients and controls

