# 7 Biometrics and sample size planning

A similar study demonstrating that peripheral facial nerve palsy impairs food intake and worsens oral hygiene, which may lead to oral diseases, was conducted at Nabon University Itabashi Hospital and Nihon University Dental Hospital in Japan from 2009 to 2011. This study included 30 patients and 30 controls. The planned study is based on this.

The necessary number of participans was determined with the Institute for Medical Statistics, Informatics and Data Science Jena. The programme G*power was used. Following values were assumed when calculating the exact number of cases:

- Wilcoxon-Mann-Whitney test (two groups)
- Tail: two
- parent distribution: min ARE
- effect size d: 0.6666667
- α err prop: 0.05
- Power (1-β err prop): 0.8
- allocation ratio N1/N2: 1

Thus, a case number of 43 patients and 43 controls was calculated. This makes a total number of 86 participants. To take drop-out cases into account, a total number of 120 subjects (60 patients/controls per group) is assumed.

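### Sections 6.6 and 6.7 analyse the OHIP-G14 question by question and name no score, so they do not deliver the single quality-of-life comparison that 1.3 and 3.2 call for

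*Protocol*

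**What the plan says.** Section 1.3 of the protocol (synopsis) lists oral health-related quality of life as the only secondary target variable. Section 3.2 names the instrument: "Secondary objective is to determine oral health-related quality of life of patients with the validated OHIP-G14 questionnaire". It then says what is to be done with it: "Results of questionnaires are compared with variables of facial nerve palsy, such as duration and cause of disease", and also with the values of a control group.

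The analysis sections set a different unit. Section 6.6 says: "With data from questionnaires, an evaluation is carried out for each question asked individually". Section 6.7 lists three questionnaire comparisons: between patients, between controls, and "answers to each question between patients and controls". All three concern answers to single questions.

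The protocol names no total score, subscale score, scoring direction or missing-item rule for the OHIP-G14. The rule in 6.6 does not separate the OHIP-G14 from Questionnaire 1, which asks about hygiene habits and risk factors (6.2).

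**The concern.** The objective concerns one construct, and the analysis rule concerns single questions. Fourteen separate item results do not add up to one estimate of the patient-control difference in quality of life. Nor do they give one quantity to relate to duration and cause of palsy.

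Two consequences follow if the items are tested. Unadjusted, some item may differ by chance and be reported as an effect on quality of life. Adjusted, each item may have little power for a moderate effect that a pooled score would show better. Without a score fixed in advance, the items to emphasise could also be chosen after the data are seen.

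**Working it through.** **1. Set the sections side by side.**

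| Section | Unit |
| --- | --- |
| 1.3 | quality of life as one secondary target variable |
| 3.2 | questionnaire results against duration, cause and control values |
| 6.6 | each question individually |
| 6.7 | answers to each question, in all three comparisons |

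For the oral indices, 6.7 gives a whole-mouth comparison as well as comparisons by side. For the questionnaires it gives no whole-scale comparison. This mismatch needs no numerical assumption.

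**2. Reproduce the plan's own figure.** Inputs from section 7: Wilcoxon-Mann-Whitney test, two-sided, min ARE (0.864), "α err prop: 0.05", "Power (1-β err prop): 0.8", "effect size d: 0.6666667", allocation 1:1. Power comes from the noncentral t distribution with
- degrees of freedom = 2 × 0.864 × n − 2
- noncentrality = d × √(0.864 × n / 2)

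At n = 42 power is 0.7998. At n = 43 the noncentrality is 0.6667 × √18.576 = 2.873 and power is 0.809. The smallest adequate n is therefore 43 per group, as stated. The same method is used below.

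**3. False positives if all items are tested.** The count of 14 is read from the instrument's name, "Oral Health Impact Profile-Germany 14". For independent tests at 0.05:
- chance of at least one false positive = 1 − 0.95^14 = 0.512
- expected number = 14 × 0.05 = 0.7

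Items of one scale are likely to correlate. The protocol gives no correlation, so a range is assumed. Simulation with 14 equally correlated normal test statistics (400,000 replicates) gives:

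| Correlation of tests | At least one false positive |
| --- | --- |
| 0 | 51% |
| 0.3 | 44% |
| 0.5 | 35% |
| 0.7 | 25% |

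**4. Power, illustration only.** Assumptions not in the protocol: every item differs by 0.3 SD, all pairs of items correlate equally at r, and all 60 per group are analysed.

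- Item: noncentrality = 0.3 × √(0.864 × 60 / 2) = 1.527; power 33%. With Bonferroni (0.05/14 = 0.0036), 8%.
- Sum score: its mean difference is 14 × 0.3 item SDs and its SD is √(14 × (1 + 13r)) item SDs, so d = 0.3 × √(14 / (1 + 13r)).

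| r | d of sum score | Power, sum score | Power, one item |
| --- | --- | --- | --- |
| 0.3 | 0.51 | 72% | 33% |
| 0.5 | 0.41 | 54% | 33% |
| 0.7 | 0.35 | 43% | 33% |

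**5. The same comparison from the protocol's effect size.** Section 7 does not tie d = 0.667 to an endpoint. If it applied to the total score, that score would have power 92% at 60 per group. The implied item effect is 0.667 × √((1 + 13r)/14):

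| r | Item d | Item power, unadjusted | Item power, Bonferroni |
| --- | --- | --- | --- |
| 0.3 | 0.39 | 51% | 17% |
| 0.5 | 0.49 | 69% | 32% |
| 0.7 | 0.57 | 81% | 46% |

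With equal item effects and equal correlations, an item has less power than the sum at every r shown. The gap narrows as r rises.

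**The case against.** **The text does not exclude a score.** Section 6.6 says that each question is evaluated; it does not say that nothing else is. Scoring rules are often left to the analysis plan, which is not available here, and the wording of 1.3 and 3.2 is compatible with a score. This stands. A reader might infer that the sponsor has decided against a score, but the protocol does not say so. What remains is that the two sections that state the analysis give a rule, and that rule does not serve the objective.

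**No item tests are announced.** A reader might also infer that 14 p-values are planned. Sections 6.6 and 6.7 speak of evaluation and comparison. The synopsis plans both descriptive and inferential statistics without assigning either to the questionnaire items. This stands too, so the false-positive figures apply only if each item is tested at 0.05 without adjustment.

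**Item tests need not be weak.** The 0.3 SD effect has no source in the protocol. An item with the full d = 0.667 would have power 92% unadjusted and 66% with Bonferroni at 60 per group. At r = 0.7 in the illustration, the sum score gains only ten percentage points (43% against 33%), and it stays below 80% throughout. The powers also assume 60 analysed per group, whereas section 7 calculates 43 and adds the rest for drop-out. All of this stands, so low power cannot carry the point.

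**Weight.** This is a secondary variable in an observational cross-sectional study, and a score could be computed later from the item data. That makes correction cheap, but a score chosen after the data are seen is not prespecified.

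**Conclusion.** The point holds as a mismatch within the protocol. Sections 6.6 and 6.7 prescribe question-by-question handling and name no OHIP-G14 score, while 1.3 and 3.2 require one quality-of-life variable to be compared with controls and related to duration and cause. That conclusion rests on the text alone.

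The size is conditional. With unadjusted tests of all 14 items, the chance of at least one false positive is 25% to 51% over assumed test correlations from 0.7 down to 0. The power advantage of a sum score ranges from large to modest, depending on an assumed item effect and inter-item correlation, and is illustrative. The documents do not support saying that a score is ruled out, that 14 significance tests are planned, or that item tests are weak in every case.

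**What to change.** In 6.6 and 6.7:
- Name one OHIP-G14 sum score per person as the secondary variable, with its scoring direction and a missing-item rule.
- Make one patient-control comparison of that score, and relate it to duration and cause of palsy as 3.2 says.
- Report the 14 items descriptively, without p-values.
- Leave the question-by-question evaluation of Questionnaire 1 unchanged.

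The cost is a short paragraph of protocol text. The item answers are already collected, so no new data, visits or participants are needed. The protocol does not describe how the OHIP-G14 is scored, so the scoring and missing-item rules should be taken from the instrument's own documentation and cited.

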## 6.7 Comparison of results

Data are first compared between patients and secondary with those of controls.

Comparisons are made with regard to oral health parameters:

- per patient:

- paretic and non-paretic side of mouth

- per controls:

- right and left side of mouth

- between patients:

- both halves of total mouth

- paretic side of mouth

- non paretic side of mouth

- between patients and controls:

- both sides of total mouth

- paretic side of mouth with corresponding side of mouth of control person

- non-paretic side of mouth with corresponding side of mouth of control person

- compared in terms of data from questionnaires:

- answers to each question between patients

- answers to each question between controls

- answers to each question between patients and controls

## 6.8 Tabular schedule

| 1. | information about the study and obtaining informed consent |
| --- | --- |
| 2. | handing out, answering and documentation of the 1st questionnaire  (Questionnaire 1, subjective assessment of own oral hygiene and oral health) |
| 3. | data collection during dental oral examination |
| 4. | documentation of data |
| 5. | handing out, answering and documentation of the 2nd questionnaire  (OHIP-G14 questionnaire on oral health-related quality of life) |
| 6. | analysis and evaluation of data |
| 7. | comparison of results |
| 8. | publication of results |

# 7 Biometrics and sample size planning

A similar study demonstrating that peripheral facial nerve palsy impairs food intake and worsens oral hygiene, which may lead to oral diseases, was conducted at Nabon University Itabashi Hospital and Nihon University Dental Hospital in Japan from 2009 to 2011. This study included 30 patients and 30 controls. The planned study is based on this.

The necessary number of participans was determined with the Institute for Medical Statistics, Informatics and Data Science Jena. The programme G*power was used. Following values were assumed when calculating the exact number of cases:

- Wilcoxon-Mann-Whitney test (two groups)
- Tail: two
- parent distribution: min ARE
- effect size d: 0.6666667
- α err prop: 0.05
- Power (1-β err prop): 0.8
- allocation ratio N1/N2: 1

Thus, a case number of 43 patients and 43 controls was calculated. This makes a total number of 86 participants. To take drop-out cases into account, a total number of 120 subjects (60 patients/controls per group) is assumed.

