## 1.2 Summary

Facial nerve palsy lead to immobility of the affected side of face (Trepel, 2017). Assumable, food residues on tooth surfaces cannot be removed by natural self-cleaning mechanisms such as targeted muscle movements or saliva, which are described in literature (Elferich & Tittmann, 2004). In addition to food intake, oral hygiene is impaired in patients (Jakobsen & Sticher, 2015). Deterioration of oral hygiene increases the risk of oral infections and consequently of other diseases (Hellwege, 2018).

Aim of this study is to investigate the oral health and oral health-related quality of life of patients with different forms of facial nerve palsy, as well as oral health in relation to facial nerve palsy variables such as disease duration and cause, which are collected as part of routine investigation at Facial Nerve Centre Jena.

In a controlled cross-sectional study, oral health parameters and oral health-related quality of life will be investigated at one time. Since patients in different temporal stages (acute phase, chronic phase) are to be documented, the setting of the Ears-, Nose- and Throat (ENT-) clinic Jena was chosen. There are both patients, with acute paresis and patients with chronic forms of facial nerve palsy. Oral health parameters and oral health-related quality of life of these patients groups should be compared with a control group. For this, controls without facial nerve palsy ever diagnosed by a doctor will be matched with corresponding patients according to age and gender.

Primary criterion for assessment of oral health will be the assessment of periodontal health, which will be analysed by a dentist using parodontal screening index (PSI; Hellwege, 2018; Weber, 2017). Other established indices are used to record caries and plaque incidence, bleeding tendency of gingiva, abnormalities of oral mucosa and presence of halitosis. These indices are compared between the two groups. Oral health-related quality of life will be assessed using the validated OHIP-G14- questionnaire (John, 2002; Slade 1997).

It is assumed a case number of 60 patients and 60 controls.

Both study groups will be recruited from ambulance level and ward level of ENT-clinic at Jena University Hospital. For better comparability, further controls can be recruited from the tinnitus centre of ENT-clinic Jena as well as from dental practices established in Thuringia.

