**Controls**

- multimorbid subjects
- age and gender mismatch with previously studied patients
- diagnosed facial nerve palsy currently or in past
- lack of consent from control or legal guardian (for subjects under 18 years of age) to participate in study
- edentulous
- suffering from one of following diagnosed diseases: Haemophilia A and B, Epilepsy, Aids

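### Controls are matched to patients on age and gender, but the only test named and powered treats the groups as independent, and no stated analysis accounts for the matching

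*Protocol*

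**What the plan says.** Matching appears in several places. Section 1.2 states that "controls without facial nerve palsy ever diagnosed by a doctor will be matched with corresponding patients according to age and gender". Section 4.3 repeats that age and gender are the matching factors. Section 5.1 has controls chosen by age and sex against patients already examined, and Section 5.2 excludes a control for "age and gender mismatch with previously studied patients". Group sizes are equal, 60 and 60. Section 6.7 compares the "paretic side of mouth with corresponding side of mouth of control person".

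The only test named anywhere is in Section 7, among the G*Power inputs: "Wilcoxon-Mann-Whitney test (two groups"), two-tailed, with "parent distribution: min ARE", "effect size d: 0.6666667", "α err prop: 0.05" and "Power (1-β err prop): 0.8". The result is 43 per group, raised to 60 per group for drop-out. The synopsis (1.3) promises descriptive and inferential statistics without naming a method. Sections 6.6 and 6.7 list comparisons but no test. No section gives a within-pair correlation, an adjustment for the matching factors or a rule for incomplete pairs. The identification list in Section 8.1 mentions no link between a control and a patient.

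**The concern.** Matching on age and gender makes the two groups alike on those factors. Where an outcome depends on them, patient and control values move together. The variance of the group difference is then smaller than an independent-samples test assumes. A raw two-group test keeps the larger variance, so its p-values are too large and the recruitment effort spent on matching brings no gain in precision.

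Enrolment is open to all ages, including minors (Section 5.1), and the sponsor chose age as a matching factor, so some positive correlation is a reasonable expectation. The protocol does not give its size.

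At stake are the efficiency of the main patient-control comparison and the meaning of the power statement in Section 7, which was derived for a design without matching.

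**Working it through.** **Inputs.** From Section 7: d = 0.6666667, two-sided alpha 0.05, power 0.80, allocation 1:1, min ARE (asymptotic relative efficiency 0.864). Assumed: the within-pair correlation r, which the protocol does not give. The range shown is 0 to 0.5, with -0.1 as a check on direction.

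**Step 1: reproduce the stated size.** For two independent groups under the ARE method, df = 2 × 0.864n − 2 and noncentrality = d × √(0.864n/2).
- n = 42: noncentrality 2.840, power 0.7998.
- n = 43: df 72.3, noncentrality 2.873, power 0.809.

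So 43 per group is correct for the test named. With 60 per group the power is 0.92.

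**Step 2: effect of ignoring a correlation r.** The standard error of a difference in means is proportional to √2 if pairing is ignored and to √(2(1−r)) in truth. Hence:
- standard-error ratio = 1/√(1−r)
- true two-sided error = 2Φ(−1.96/√(1−r))

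This approximation was set against a simulation of the Mann-Whitney test (normal data, 43 pairs, 4000 runs).

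| r | SE ratio | Error, formula | Error, simulated |
|---|---|---|---|
| 0 | 1.00 | 5.0% | 5.0% |
| 0.1 | 1.05 | 3.9% | 4.6% |
| 0.2 | 1.12 | 2.8% | 3.2% |
| 0.3 | 1.20 | 1.9% | 2.2% |
| 0.5 | 1.41 | 0.6% | 0.7% |

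**Step 3: size and power of a paired analysis.** For the signed-rank test with the same ARE, dz = d/√(2(1−r)), df = 0.864n − 1 and noncentrality = dz × √(0.864n).

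| r | dz | Pairs for 80% | Power, 43 pairs | Power, 60 pairs | Power, 31 pairs |
|---|---|---|---|---|---|
| −0.1 | 0.449 | 48 | 0.76 | 0.89 | 0.61 |
| 0 | 0.471 | 44 | 0.80 | 0.92 | 0.65 |
| 0.1 | 0.497 | 40 | 0.84 | 0.94 | 0.70 |
| 0.2 | 0.527 | 35 | 0.88 | 0.96 | 0.75 |
| 0.3 | 0.563 | 31 | 0.92 | 0.98 | 0.80 |
| 0.5 | 0.667 | 23 | 0.98 | >0.99 | 0.91 |

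In the simulation with 43 pairs and r from 0 to 0.5, Mann-Whitney power was 0.85 to 0.92 and signed-rank power 0.84 to 0.99. The unpaired test therefore still reaches its planned power when r is zero or more.

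**Step 4: what drop-out does to pairs.** Going from 60 to 43 allows a loss of 1 − 43/60 = 28.3% per person. If losses are independent and not replaced, complete pairs number 60 × (43/60)² = 30.8, about 31. The last column shows that a strictly paired test then has 80% power only if r is about 0.3 or more. The unpaired test on the remaining 43 per group keeps 0.81.

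**The case against.** The strongest reply is that the protocol fixes no analysis. The Mann-Whitney test appears only as a planning assumption, and a statistical analysis plan that is not shown could specify a paired or adjusted comparison. That stands in part: it would be wrong to say that the final analysis will ignore the matching. What remains is that the power statement is fixed in the protocol and assumes a design other than the one described.

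A reader might infer that the design is definitely 1:1 pairs. The reference to corresponding patients in Section 1.2 and the equal numbers point that way, but no section speaks of pairs, an age tolerance or a pair identifier. Section 4.3 says only that the study is matched, and the selection criteria refer to patients in the plural. The corresponding side in Section 6.7 may simply mean left with left and right with right. Group matching is a possible reading, and under it a signed-rank test has no defined pairs.

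A reader might also infer that reported intervals will be too wide. The protocol specifies no intervals, and the effect is nil at r=0, about 5% at r=0.1, and reversed if r is negative.

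Finally, a paired test might look free because 44 pairs at r=0 is almost 43. It is not free once partners are lost, as the 31-pair column shows.

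**Conclusion.** The point holds as an inconsistency between design and planned test: controls are matched on age and gender, the only test named and powered is for independent groups, and nothing stated accounts for the matching. Its size depends on an assumed r. At r=0 nothing is lost. At r=0.2 the true error is 2.8% with standard errors 12% too large, and at r=0.5 it is 0.6% with standard errors 41% too large.

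For r of zero or more the fault is conservative. It creates no excess of false positives and does not show the study to be underpowered. Someone might take the difference between 43 per group and the paired sizes as proof of a wrong sample size. The figures do not support this: 43 is right for the test named, 60 per group are to be enrolled, and for positive r fewer pairs than that would suffice. The point is therefore a cheap improvement and ranks below a mandatory correction.

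**What to change.** 1. In Sections 4.3 and 5.1, state whether matching is individual or by group, and give the age tolerance.
2. In Sections 6.7 and 7, state that the patient-control comparison accounts for the matching factors. Make the default an ordinal regression of the outcome on group with age and sex as covariates. It keeps every participant and is valid under either form of matching.
3. If matching is individual, record a pair identifier at recruitment. A model with a pair effect or a Wilcoxon signed-rank test can then serve as the primary or supporting analysis, with a stated rule for incomplete pairs.
4. In Section 7, say that 43 per group is an independent-groups figure, and show the paired equivalents with r labelled as an assumption: 44 pairs at r=0, 31 at r=0.3, 23 at r=0.5.

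The cost is protocol wording, one column in the Excel file and one recalculation; age and sex are already needed for the matching. The drawback of a strictly paired primary test is the loss of participants without a partner, which at the allowed 28.3% loss could leave about 31 of 60 pairs. For that reason the covariate-adjusted model is the safer default.
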